## Safety and adverse events

Data on adverse events and suicidal ideation will be collected by blinded independent raters bi-weekly during treatment, at post-treatment and at 3- and 12-month follow-up. Adverse

events will be collected using a standardized checklist, the Safety Monitoring Uniform Report Form (SMURF).(43) If a participant expresses suicidal ideation (i.e. a score on item 9 of the MADRS-S  $\geq 4$ ), assessors will initiate a structured suicide risk assessment. If there is an urgent need for psychiatric care, a trial psychiatrist will contact participants to schedule a face-to-face appointment as soon as possible.

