## METHODS AND ANALYSIS

### **Study design**

Single-blind, randomized controlled non-inferiority trial comparing therapist-guided ICBT, unguided ICBT without therapist support, and individual f2f CBT for OCD in adults. The total number of participants will be 120 (40 per group), with stratification according to source of referral (self- vs. clinic referred patients). Block randomization will be performed within each stratum to ensure all participants are equally represented across treatment conditions. Participants will be assessed at baseline, bi-weekly during treatment, at post-treatment, and at 3- and 12-months follow-ups. The CONSORT flowchart of the trial is depicted in Figure 1.

[figure not shown]

Figure 1: Participant flow in the study

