### **Measurements**

Table 2 lists clinician-rated and self-rated assessments at the different time points. The primary outcome measure is the clinician-rated Yale-Brown Obsessive Compulsive Scale (Y-BOCS), the gold standard for assessing the severity of OCD symptoms.(32) Clinicians in this trial will practice together on case examples to establish high inter-rater reliability. The Y-BOCS will be administered by blind raters at baseline, at weeks 2, 4, 6, 8, 10 and 12 during treatment, at post-treatment (week 15), and at 3- and 12-months follow-ups. The primary endpoint is the 3-month follow-up.

Secondary clinician-administered outcome measures are the Clinical Global Impression – Severity and Improvement scale (CGI-S, CGI-I),(33) the Structured Clinical Interview for DSM-5 (SCID-5), obsessive–compulsive and related disorders,(28) and the Global Assessment of Functioning (GAF).(34) Secondary self-rated outcome measures are the Obsessive-Compulsive Inventory (OCI-R),(35) the self-rated Y-BOCS,(32) the Montgomery-Åsberg Depression Rating Scale (MADRS-S),(36) Sheehan Disability Scale (SDS)(37) and the Euroqol (EQ-5D).(38) The Patient Exposure/Responsiveness Adherence Scale (PEAS)(39) will be used to quantify compliance with ERP homework and the Working Alliance Inventory – Short Form (WAI-SF)(40) will be used to measure therapeutic alliance in the face-to-face CBT and ICBT with therapist support treatment conditions. The Insomnia Severity Index (ISI)(41) will be used to measure participants sleep patterns and the Treatment

Credibility Scale (TCS)(42) will be used to measure how credible participants perceive the treatment to be. Measurements will be administered before and after treatment as well as during 3- and 12 months follow-ups. In order to increase participant retention at follow-up assessments, participants will be notified via text message 48 hours prior to an appointment. Should a participant not attend a follow-up session, a psychiatrist will contact participants via telephone to perform the assessments.

| Table 2. Assessments at different time points |           |               |                  |                |                   |                    |
|-----------------------------------------------|-----------|---------------|------------------|----------------|-------------------|--------------------|

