### **Patient and public involvement**

We received input from patients from three previous OCD internet CBT trials which guided the design of the current study. In the current trial, no patients were involved in the design of the study or in the decision of outcome measures. Neither will patients be involved in the recruitment of participants or in the decision of the research question. A patient organization for OCD and related disorders (the Swedish OCD Foundation) will be involved in the recruitment of participants by informing their members about the study. We will assess the burden of the trial interventions on the patients by collecting information about adverse events, quality of life, and time spent on the treatment. We will gather information about the patients satisfaction with treatment through an online self-rating questionnaire at the end of treatment. We plan to disseminate the results of the research to study participants and to the Swedish OCD Foundation.

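### The adverse-event checklist is scheduled only once treatment is under way, and the plan states no way to separate complaints already present from new or worsened ones

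*Combined protocol and SAP*

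**What the plan says.** The section Safety and adverse events gives the timing: data on adverse events and suicidal ideation are "collected by blinded independent raters bi-weekly during treatment, at post-treatment and at 3- and 12-month follow-up". The instrument is named in the next sentence: "events will be collected using a standardized checklist, the Safety Monitoring Uniform Report Form (SMURF").

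Table 2 agrees. The SMURF row is empty under Screening and Pre treatment and marked in the four later columns. The week of the first SMURF is not stated. The clinician-rated Y-BOCS is given "at baseline, at weeks 2, 4, 6, 8, 10 and 12 during treatment, at post-treatment (week 15"), so week 2 is the natural inference for a form on the same two-weekly cycle.

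Under Patient and public involvement the data are given a purpose: "We will assess the burden of the trial interventions on the patients by collecting information about adverse events", alongside quality of life and time spent on treatment. The Statistical analysis section covers outcome measures and does not mention adverse events. Nowhere is there a definition of a treatment-emergent event, a rule for onset or worsening, or a causality rating.

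**The concern.** Complaints such as poor sleep, low mood or anxiety can be present at entry in patients with OCD. If a checklist records one of them at the first treatment call, the plan offers no stated basis for calling it new, worse or unchanged. All three arms receive active CBT, so no untreated arm supplies a background rate.

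Other rows of Table 2 without a pre-treatment mark mostly have a reason for it: improvement, homework adherence, treatment credibility and alliance do not exist before treatment. Checklist complaints can. The symptom and function measures used as outcomes (Y-BOCS, CGI-S, GAF, self-rated MADRS-S, SDS, ISI, EQ-5D) all have a pre-treatment value.

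Two things are at stake. One is the meaning of the event rate within each arm, and so of the burden statement. The other is the precision with which the arms can be compared on harms, including the arm that has no therapist support.

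**Working it through.** **Schedule check.** The text lists four kinds of occasion (two-weekly during treatment, post-treatment, 3 months, 12 months). The Table 2 row marks the same four columns and no others. The two sources match, so the missing pre-treatment form is the plan as written and not a slip in one place. The plan states no harms figure to reproduce.

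**Illustration.** Inputs:
- n = 40 per arm, from Study design: "The total number of participants will be 120 (40 per group").
- b = share of patients with a given complaint before treatment. Assumed, range 10% to 50%.
- e₁ = 10% and e₂ = 30% = share of the remaining patients who newly develop it in two arms. Assumed.
- Pre-existing complaints persist and are recorded; everyone is assessed; two-sided alpha 0.05.

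Formulas:
- Recorded rate in arm i: rᵢ = b + (1 − b)eᵢ
- New-event rate among all randomised: nᵢ = (1 − b)eᵢ
- Inflation of the within-arm rate: rᵢ − nᵢ = b
- Arm difference: r₂ − r₁ = n₂ − n₁ = (1 − b)(e₂ − e₁), the same on both counts
- SE = √[(p₁(1 − p₁) + p₂(1 − p₂))/40]; power = Φ(difference/SE − 1.96)

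At b = 50%:
- Recorded: 0.50 + 0.50 × 0.10 = 0.55 and 0.50 + 0.50 × 0.30 = 0.65. SE = √[(0.2475 + 0.2275)/40] = 0.109. Power = Φ(0.10/0.109 − 1.96) ≈ 0.15.
- New: 0.50 × 0.10 = 0.05 and 0.50 × 0.30 = 0.15. SE = √[(0.0475 + 0.1275)/40] = 0.066. Power = Φ(0.10/0.066 − 1.96) ≈ 0.33.

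A pooled-variance test gives 0.15 and 0.32, so the choice of formula does not matter here.

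| Assumed b | Pre-existing per arm | Recorded rates | New rates | Difference (both) | Power, recorded | Power, new |
|---|---|---|---|---|---|---|
| 10% | 4 | 19% vs 37% | 9% vs 27% | 18 points | 0.45 | 0.58 |
| 20% | 8 | 28% vs 44% | 8% vs 24% | 16 points | 0.33 | 0.52 |
| 30% | 12 | 37% vs 51% | 7% vs 21% | 14 points | 0.25 | 0.45 |
| 50% | 20 | 55% vs 65% | 5% vs 15% | 10 points | 0.15 | 0.33 |

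The within-arm rate is too high by b itself. The arm difference is unchanged, but its standard error is larger on recorded events.

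**The case against.** The strongest reply is that the content of SMURF is not in the documents. The form may ask about onset, change or attribution; if it does, much of the gap closes. This stands, and it is why the point is that the plan states no means of separation, not that separation is impossible.

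Other information also covers part of the gap. A psychiatrist conducts the MINI and SCID-5 and documents comorbidities before inclusion. Self-rated MADRS-S, SDS and EQ-5D are taken at screening and pre-treatment, and ISI at pre-treatment. The two-weekly repeats show when a complaint first appears after the first call. So the ambiguity falls mainly on complaints already present at that call. This too stands, though these measures cover mood, sleep, function and diagnoses and cannot be assumed to match the checklist items.

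Three stronger readings are tempting, and the documents do not support them:
- That the comparison of harms between arms is biased. Randomisation balances pre-existing complaints in expectation, and raters are blinded and follow one schedule in every arm. The cost is precision.
- That the non-inferiority conclusion is weakened. Non-inferiority is defined on the Y-BOCS alone, and no section makes it depend on comparable harms.
- That a baseline form would recover the full 20-point difference (power about 0.6) that would apply if nobody had the complaint at entry. A patient who already has it cannot newly develop it, so the difference among all randomised stays at (1 − b) × 20 points.

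**Conclusion.** The point holds as a gap in how harms can be interpreted, and it merits a change to the plan. Text and table agree that the checklist is scheduled only from the treatment phase, and nothing in the documents says how complaints present beforehand are to be handled. Within-arm rates and the burden statement would then include them. Under the assumed 10% to 50% prevalence, that is 4 to 20 patients per arm of 40 for a given complaint. At 50%, counting new events instead of all recorded ones raises power for the same 10-point difference from about 0.15 to about 0.33. That is a real gain, but harms comparisons remain underpowered either way.

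The size rests on assumed prevalences, on persistence of pre-existing complaints, and on a form whose items and recall period cannot be seen. Week 2 as the first administration is inferred. The primary Y-BOCS analysis is not affected.

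**What to change.** 1. For participants still to be enrolled, mark SMURF in the pre-treatment column of Table 2 and give it at the existing baseline assessment, before allocation is known.
2. Define an adverse event for reporting as a complaint that is new, or worse, relative to that record.
3. For participants already enrolled, use the onset recorded at each SMURF and class complaints that began before treatment as pre-existing. If the form does not capture onset, say so and add it to the remaining assessments. Use pre-treatment ISI and MADRS-S as a partial check on sleep and mood only.
4. Report by arm, separately up to 3 months and from 3 to 12 months. Under Interventions, ICBT non-responders are offered f2f CBT at the 3-month follow-up, so later events cannot be read by original arm alone.

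The cost is a few minutes at an existing visit and a short written definition. The benefit of step 1 is limited: recruitment began in September 2015 and the last participant is due at 3 months in February 2019, so few may remain to be enrolled and a baseline form cannot help those already treated. Steps 2 to 4 can still be fixed before the primary analysis starts in April 2019.

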### **Statistical analysis**

The main outcome analyses will be conducted according to the “intent-to-treat” principle. Mixed-effects regression analyses for repeated measures with maximum likelihood estimation (MLE) of parameters will be used with the assumption that data are missing at random. The latter assumption will be tested. For each outcome measure, the model will include fixed effects of time (baseline, mid-treatment, post-treatment, and 3-month follow-up [primary endpoint]), treatment group (guided ICBT, unguided ICBT, f2f CBT) and an interaction effect of treatment group x time to allow for the differential change between the three groups from baseline to the 3-month follow-up. The models will include individuals’ random intercept and random slope to account for variability between and within participants over time. Within- and between-group effect sizes will be calculated with Cohen’s *d*.(44) Numbers needed to treat will be calculated based on responder status.

Alpha for all analyses will be set at 0.05. Non-inferiority is established when the 90% Wald confidence interval for the difference between treatment conditions excludes the pre-specified margin of inferiority, which is set at 3 points on the Y-BOCS (45, 46). This means that if the upper limit of the 90% confidence interval is less than 3 points, we are 95% confident that ICBT will be non-inferior to f2f CBT. The non-inferiority hypothesis will be tested of both therapist-guided and self-guided ICBT against the f2f CBT. Additional analyses of the 12-month follow-up data will determine whether the treatment gains are maintained long-term and whether ICBT is non-inferior to f2f CBT at follow-up.

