## ABSTRACT

**Introduction** Expert guidelines recommend cognitive behaviour therapy (CBT) as a first line treatment for Obsessive-Compulsive Disorder (OCD) but the majority of patients with OCD do not have access to CBT. Internet-delivered CBT (ICBT) has the potential to make this evidence-based treatment more accessible whilst requiring less therapist time than traditional face-to-face (f2f) CBT. Data from six clinical trials suggests that ICBT for OCD is both efficacious and cost effective but whether ICBT is non-inferior to traditional f2f CBT for OCD is yet unknown.

**Methods and analysis** A single-blind, randomized controlled non-inferiority trial comparing therapist-guided ICBT, unguided ICBT, and individual (f2f) CBT for adult OCD patients. The primary objective is to investigate whether ICBT is non-inferior to gold standard f2f CBT. Secondary objectives are to investigate if ICBT is equally effective when delivered unguided, to establish the cost-effectiveness of ICBT, and to investigate if the treatment outcome differs between self-referred and clinically-referred patients. Participants will be recruited at two specialist OCD clinics in Stockholm, and also through online self-referral. Participants will be randomized to one of three treatment conditions: F2f CBT, ICBT with therapist support or unguided ICBT. The total number of participants will be 120 and masked assessments will be administered at baseline, bi-weekly during treatment, at post-treatment, and at 3- and 12-months follow-ups. The main outcome measure is the clinician-rated Yale-Brown Obsessive Compulsive Scale (Y-BOCS) at 3-month follow-up. The margin of non-inferiority is set to 3 points on the Y-BOCS using a 90% confidence interval.

**Ethics and dissemination** The study has been approved by the Regional Ethics Board of Stockholm (REPN 2015/1099-31/2) and registered at Clinicaltrials.gov (NCT02541968). The study will be reported in accordance with the CONSORT statement for non-pharmacological trials. The results will be published in peer-reviewed academic journals and disseminated to patient organizations and media.

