### **Sample size calculation**

In order to provide accurate estimates for the power calculation in the current trial, we will use individual-level data from a previous study of therapist-guided ICBT with identical Y-BOCS assessments by blinded raters and six repeated observations.(14) To calculate the required sample size, we used a bootstrap simulation with 1000 samples using the following assumptions, based on data from the previous trial: a variance of the random intercept of 10.5, a variance for the random slope of 0.04, and a within- individual residual variance of 20.4. With 3 treatment groups and 8 observations (Y-BOCS) per patient, we estimated that a total of 120 participants would be needed to detect a slope difference between two groups (i.e. group 1 vs. group 2 and group 1 vs. group 3) of 3 points at 3-month follow-up with over 90% power. We will request an interim power analysis by the Karolinska Trial Alliance to test these assumptions, using data from 80 individuals, and adjust sample size if power is lower than anticipated (see supplementary file 1 for a detailed description).

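### The plan names the 3-month visit as primary but not the model contrast tested against the 3-point margin, and its power, visit schedule and analysis model imply different ones

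*Combined protocol and SAP*

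**What the plan says.** **Endpoint.** The Abstract states: "The main outcome measure is the clinician-rated Yale-Brown Obsessive Compulsive Scale (Y-BOCS) at 3-month follow-up". Measurements agrees: "The primary endpoint is the 3-month follow-up".

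**Decision rule (Statistical analysis).** "Non-inferiority is established when the 90% Wald confidence interval for the difference between treatment conditions excludes the pre-specified margin of inferiority", with the "pre-specified margin of inferiority, which is set at 3 points on the Y-BOCS". The rule does not say whether the difference is a slope, a change or a level, or how time is coded.

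**Model (Statistical analysis).** It has "fixed effects of time (baseline, mid-treatment, post-treatment, and 3-month follow-up [primary endpoint", treatment group, their interaction running from baseline to 3 months, and a random intercept and slope per person. That is four named occasions.

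**Sample size calculation.** The 120 participants are needed "to detect a slope difference between two groups" of 3 points at 3 months, with 8 observations per patient and power above 90%. The variances are 10.5 (intercept), 0.04 (slope) and 20.4 (residual). No time unit is given for the slope.

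**Measurements.** Y-BOCS is rated at baseline and "at weeks 2, 4, 6, 8, 10 and 12 during treatment, at post-treatment (week 15), and at 3- and 12-months follow-ups". Up to 3 months that makes 1 + 6 + 1 + 1 = 9 ratings.

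**Supplement (interim power analysis).** The code fits time as a second random intercept, and the results label its variance, 10.02, as a random slope. This does not settle how time enters the model.

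**The concern.** An analyst could fit a linear slope, a fitted level from a linear model, or a categorical 3-month contrast, and claim to have followed the plan each time. These are different quantities when change is not linear.

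Linearity is doubtful here. The period covers 14 weeks of treatment followed by three months after it, and face-to-face sessions run twice weekly only in the first two weeks, so the arms could separate early.

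In a non-inferiority trial, a contrast that understates the deficit at the primary visit raises the chance of a false claim. The choice also decides whether the stated power applies to the test that is run.

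**Working it through.** **Inputs.** 40 per arm (Study design); variances 10.5, 0.04 and 20.4 (Sample size calculation); visits at weeks 0, 2, 4, 6, 8, 10, 12 and 15 (Measurements); margin 3 and a 90% interval, so one-sided 0.05 and z = 1.645 (Statistical analysis). Assumptions: 3-month visit at week 28, complete data, variances known, intercept and slope uncorrelated.

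**1. The plan's power figure.** For a linear group-by-time slope scaled to the last visit T, with separate intercepts:

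SE = T × √[(2/40) × (20.4/SSx + 0.04)], power = Φ(3/SE − 1.645).

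- Weeks, 9 visits: SSx = 570.2, SE = 28 × √(0.05 × 0.0758) = 1.72, power 54%.
- Months, 9 visits (4.345 weeks per month): SE = 1.22, power 79%.
- Visit number, 9 visits: SSx = 60, SE = 8 × √(0.05 × 0.38) = 1.10, power 86%.
- Visit number, 8 visits: SSx = 42, SE = 7 × √(0.05 × 0.5257) = 1.13, power 84%.

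Among the codings tried with 40 per arm and slope variance 0.04, power above 90% appears only with visit numbers, and then only with a common intercept (93.2%, 8 visits) or the fitted level at the last visit (90.1%, 8 visits). Without the time unit, the stated figure is neither confirmed nor refuted.

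**2. What a straight line does to a true 3-month deficit of 3.** Let d be the true group difference at each visit.

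Estimate = T × Σ(t − t̄)d / SSx; false non-inferiority = Φ((3 − estimate)/SE − 1.645).

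Example: f2f leads by 3 from week 2 on. In weeks t̄ = 9.444, so the estimate is 28 × 3 × 9.444/570.2 = 1.39, and Φ((3 − 1.39)/1.72 − 1.645) = 24%. By visit number t̄ = 4, so the estimate is 8 × 3 × 4/60 = 1.60, and Φ((3 − 1.60)/1.10 − 1.645) = 35%.

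Each cell gives the estimate and the false non-inferiority rate (nominal 5%):

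| Deficit reaches 3 | Slope × T, weeks | Slope × T, visit number | Fitted level, weeks | Fitted level, visit number |
|---|---|---|---|---|
| by week 2, then flat | 1.39, 24% | 1.60, 35% | 3.59, 2% | 3.47, 2% |
| by week 4, then flat | 1.94, 15% | 2.20, 18% | 3.79, 2% | 3.60, 1% |
| by week 8, then flat | 2.74, 7% | 3.00, 5% | 3.98, 1% | 3.67, 1% |
| by week 15, then flat | 3.23, 4% | 3.17, 4% | 3.74, 2% | 3.19, 3% |
| only after week 15 | 2.73, 7% | 1.60, 35% | 2.14, 13% | 1.13, 57% |

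The weeks columns read 0.04 as per week squared. If it is per month squared, the first row gives Φ((3 − 1.39)/1.22 − 1.645) = 37%, so 35% is not a strict ceiling.

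**3. Power of a categorical 3-month contrast, true difference 0.** Variances per person:

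- level: 10.5 + 0.04T² + 20.4
- change: 0.04T² + 2 × 20.4
- baseline-adjusted: level variance − 10.5²/30.9

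SE = √(variance × 2/40). With T = 28 weeks the variances are 62.26, 72.16 and 58.69.

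| Contrast | SE, per week² | Power | n/arm for 90% | Power, per month² or visit² | n/arm for 90% |
|---|---|---|---|---|---|
| Level | 1.76 | 52% | 119 | 75–76% | 62–64 |
| Change | 1.90 | 47% | 138 | 65–66% | 81–83 |
| Baseline-adjusted | 1.71 | 54% | 112 | 79–80% | 56–57 |

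**4. Four occasions or nine.** With categorical time and complete data, the SE of the 3-month level is 1.764 either way. With an assumed random dropout of 10%, 20% or 30%, it is 1.837, 1.922 or 2.024 with nine visits and 1.846, 1.942 or 2.056 with four. That is an increase of 0.5% to 1.6%.

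**The case against.** The strongest reply is that the Statistical analysis section lists time as named occasions, which reads most naturally as categories. The random slope then belongs to the covariance, and the 3-month interaction term cannot hide a deficit at that visit. This is a fair reading. It does not explain why a slope was powered, and the power in step 1 does not carry over to it.

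Three stronger readings are tempting, and the documents do not support them.

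- *The test is not tied to the 3-month visit.* The Abstract, Measurements and Statistical analysis all mark that visit as primary, and the sample size scales its difference to it. Only the contrast is missing.
- *The plan specifies a linear slope test with 24–35% false non-inferiority.* No sentence says that the slope is the test. Those figures also need the full 3-point gap by week 2 (or, by visit number, only after week 15) and slope × T alone. Adding the group main effect to the week-2 profile brings the error to about 2%, although late divergence is then worse. No linear version is safe for every shape.
- *The plan discards five of six bi-weekly ratings.* The model sentence covers every outcome, and Table 2 has a single during-treatment column, so mid-treatment may be shorthand for all those ratings. Even if only one were kept, the loss of precision is slight (step 4).

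**Conclusion.** The point holds as a gap between the powered contrast and the described analysis. The primary visit is fixed, but the quantity compared with the margin is not, and the counts of 8, 9 and 4 observations are not reconciled.

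If the slope is the test, false non-inferiority at a true deficit of 3 is about 4% to 24% in weeks and up to about 35% by visit number for the shapes examined, on either side of the nominal 5%. The fitted level at 3 months errs for late divergence instead (about 13% in weeks). If time is categorical there is no masking, and power at 40 per arm is about 47–54% or 65–80%, depending on the unit of the slope variance.

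These sizes rest on week 28 for the 3-month visit, the plan's own variances, complete data and one-sided 0.05. They show what the open choice could cost and do not predict the trial's error rate. The matter should be settled before the primary analysis.

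**What to change.** Define the primary contrast for each ICBT arm as the model-based mean Y-BOCS difference, ICBT minus f2f, at the 3-month visit. Use time as a categorical fixed effect, all nine scheduled ratings, preferably a common baseline mean, and either an unstructured or a random intercept-and-slope covariance. Compare that contrast's 90% interval with 3 points. With the mean at each visit left free, this holds false non-inferiority at 5% for any trajectory. Say what mid-treatment means, and restate the power for this contrast with the time unit given.

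The change is to wording, and it has two costs. The stated power will be lower. The SE is also somewhat larger than for a slope: in weeks, 1.90 for change against 1.72, recovered to 1.71 with baseline adjustment; by visit number, 1.22 against 1.10 even with baseline adjustment. Keeping every bi-weekly rating adds little precision. Its value is to support the missing-at-random assumption and to bring the analysis closer to the repeated ratings that the power calculation counts.

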### *Secondary objectives*

2. To investigate if ICBT for OCD can be delivered without therapist support without impairing efficacy.
3. To determine if ICBT, compared to f2f CBT, is a cost-effective treatment for OCD.
4. To examine if there is a difference in treatment outcome between self-referred and clinically referred patients.
5. To explore predictors and moderators of treatment outcome as a first step towards personalized treatment selection.

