## Randomization and concealment

The randomization sequence will be generated by Karolinska Trial Alliance (KTA, <https://karolinskatrialliance.se>, an independent entity not involved in the study) before inclusion of the first participant, using masked block randomization. Patients will receive their randomization number based on the order of their first psychiatrist appointment. Patients will be stratified based on self- or clinical referral. Sealed envelopes with information on treatment allocation will be stored in a secure locker in case of emergency unblinding.

Assessors will be blind to group assignment up to the 12- month follow-up. To ensure that the blinding is maintained, patients will be given clear instructions not to disclose which treatment they have been randomized to while being interviewed by the blind assessors. Where blindness is inadvertently broken, raters will be immediately replaced and the participant re-assessed by another rater. Blind raters will be asked to guess each patient's group allocation at each assessment point.(29) This will establish if the blind raters' guesses regarding treatment allocation were better than chance.

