### **Cost-effectiveness analysis**

Health economic data will be collected using the TIC-P(47) and the Swedish National Patient Register, the Swedish Prescribed Drugs Register and the longitudinal integrated data-base for health insurance and work-related research (LISA). Costs will be analysed using a societal perspective i.e. including both sick-leave, hospitalizations, service use, medication, etc. and analysed in relation to outcome (i.e. OCD symptoms and quality-adjusted life years using the Y-BOCS and EQ-5D, respectively). National tariffs will be used to estimate costs from health care visits. Productivity losses will be estimated using gross earnings data from each patient.(48) Treatment costs, i.e. therapist support time per patient logged on the platform and time spent on f2f sessions, will be included in the cost estimation.

Cost-effectiveness comparisons will be analysed using incremental cost-effectiveness ratios. The “net benefit approach” will also be used. This approach estimates the cost-effectiveness depending on different societal willingness-to-pay values for one unit of improvement.(48) Non-parametric bootstrapping (one thousand replications) will be used to estimate the difference between ICBT (guided or unguided) and gold standard f2f CBT.

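### The primary model gives each arm its own baseline mean and omits the referral-source stratum, and no analysis estimates the referral difference of secondary objective 4

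*Combined protocol and SAP*

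**What the plan says.** **Randomisation.** The Study design section describes a trial of 120 patients, 40 per group, "with stratification according to source of referral (self- vs. clinic referred patients". The Randomization and concealment section repeats it: "Patients will be stratified based on self- or clinical referral".

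**Primary model.** The Statistical analysis section lists "fixed effects of time (baseline, mid-treatment, post-treatment, and 3-month follow-up [primary endpoint", then treatment group with three levels, then "an interaction effect of treatment group x time to allow for the differential change between the three groups". It adds: "The models will include individuals’ random intercept and random slope to account for variability between and within participants over time". Referral source is not listed. Non-inferiority is judged by whether the upper limit of a 90% Wald interval for the difference between conditions lies below 3 Y-BOCS points. The section does not say whether that difference is in change from baseline or in the 3-month level, nor whether time is categorical or linear.

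**Objective 4.** Among the secondary objectives is: "To examine if there is a difference in treatment outcome between self-referred and clinically referred patients". It stands apart from objective 5, on predictors and moderators. The predictors section models binary response and remission by cross-validated AUC and names no candidate variables.

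**Economic analysis.** Bootstrapping "will be used to estimate the difference between ICBT (guided or unguided) and gold standard f2f CBT". Covariate adjustment is not mentioned.

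**The concern.** Baseline is one level of the outcome's time factor and group has its own main effect, so the model estimates three separate baseline means. A change contrast from such a model also carries the sampling error of the baseline difference between arms, which is known to be zero in expectation. The non-inferiority decision rests on one confidence limit against a 3-point margin, so an interval wider than necessary can make a treatment that truly is non-inferior fail.

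The stratum also has no place in the model, although the trial randomises by it. Objective 4 is left without a term, contrast or interval, so the choice of how to answer it would be made after the data are seen.

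**Working it through.** **Inputs.** From the Sample size calculation section: random-intercept variance g0 = 10.5, random-slope variance g1 = 0.04, residual variance s² = 20.4, 8 observations per patient, a 3-point difference, power above 90%. From Study design: 40 per arm. From Measurements: weeks 0, 2, 4, 6, 8, 10, 12, 15 and the 3-month follow-up. Assumed: follow-up at week 27 (15 + 12), zero intercept-slope covariance, no dropout. The interim components in the supplement are not used, because that code fits time as a grouping factor and not as a random slope.

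The variance of a difference between two arms is 2/40 = 1/20 of the per-patient variance. Power = Φ(3/SE − 1.645), one-sided 0.05, which corresponds to the 90% interval.

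**The plan's own figure.** The time unit of the slope variance, the covariance, sidedness and dropout are not stated, so the claim of over 90% cannot be reproduced uniquely. For a slope difference with arm-specific baselines, power is 84% (visit index 0-7), 86% (index 0-8), 80% (months) or 55% (weeks). With the endpoint contrast on visit index it is 90.1%.

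**Categorical time.** Only the first and last visits matter with complete data.
- V00 = 10.5 + 20.4 = 30.9; V0T = 10.5; VTT = 30.9 + 0.04 T².
- Weeks, T = 27: VTT = 60.06.
  - Change, free baselines: 30.9 + 60.06 − 2 × 10.5 = 69.96; SE = √(69.96/20) = 1.870.
  - Common baseline: 60.06 − 10.5²/30.9 = 56.49; SE = 1.681.
  - Endpoint, free baselines: SE = √(60.06/20) = 1.733.
- Visit index, T = 7: VTT = 32.86. By the same formulas, change 1.462, common baseline 1.210, endpoint 1.282.

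**Linear time.** Let t̄ be the mean time, Sxx the sum of squares about it and k the number of visits.
- Slope variance: A = g1 + s²/Sxx.
- Intercept variance: B = g0 + s²(1/k + t̄²/Sxx).
- Covariance: C = −s² t̄/Sxx.
- Change, free baselines: SE = T√(A/20). Common baseline: SE = T√((A − C²/B)/20).
- Weeks (9 visits, t̄ = 9.333, Sxx = 534): A = 0.0782, B = 16.09, C = −0.3566. SE 1.688 to 1.601.
- Visit index 0-7 (t̄ = 3.5, Sxx = 42): A = 0.5257, B = 19.0, C = −1.70. SE 1.135 to 0.957.
- Endpoint, free baselines: per-patient variance g0 + T²g1 + s²(1/k + (T − t̄)²/Sxx). SE 1.641 (weeks) and 1.024 (index).

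| Time coding | Change SE, free | SE, common baseline | Saving | Power | Endpoint SE, free | Saving if endpoint |
|---|---|---|---|---|---|---|
| Weeks, categorical | 1.870 | 1.681 | 10% | 48% to 56% | 1.733 | 3% |
| Weeks, linear | 1.688 | 1.601 | 5% | 55% to 59% | 1.641 | 2% |
| Index, categorical | 1.462 | 1.210 | 17% | 66% to 80% | 1.282 | 6% |
| Index, linear | 1.135 | 0.957 | 16% | 84% to 93% | 1.024 | 7% |

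Power is for the change contrast. Once the baseline is common, the change and endpoint contrasts are the same quantity.

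**Sensitivity.** With intercept-slope correlation +0.3, linear weeks go from 1.688 to 1.671 (1%). With −0.3, linear index goes from 1.135 to 0.908 (20%).

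**Stratum.** A referral effect that is constant over time drops out of a free-baseline change contrast: the SE stays at 1.135 (index) or 1.688 (weeks) whatever its size. A saving would need a referral effect on change, and the documents give none.

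**Objective 4.** Assume a 60:60 referral split, week-scale variances and a two-sided 0.05 test. SE = √(69.96 × 2/60) = 1.527 (categorical), or 1.688 × √(40/60) = 1.379 (linear). Power for 3 points is Φ(3/1.527 − 1.96) = 50% to Φ(3/1.379 − 1.96) = 59%.

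**The case against.** A group x time mixed model with free baselines is standard practice. Leaving a stratification factor out of a linear model does not bias the estimate; the interval is, if anything, too wide, which makes a non-inferiority claim harder. This stands: the point is about efficiency, not validity.

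A reader might infer that the tested contrast is a raw change score carrying all the baseline noise. The documents do not say so. With linear time and a random slope the contrast draws on every visit, and if the interval is for the 3-month level the saving is only 2-7%.

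A reader might also infer that the trial falls short of its stated power. That depends on the unstated time unit and contrast: most change-contrast readings fall below 90%, but the endpoint reading on visit index reaches 90.1%. Nor should 84% to 93% be quoted alone, since in weeks the same change moves power only from 55% to 59% (linear) or 48% to 56% (categorical).

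On objective 4, referral source could be entered as a candidate predictor. The plan does not say that it will be, and an AUC for response would not estimate a difference in outcome between referral groups.

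On the QALY comparison, the plan is silent. It does not state that the bootstrap is unadjusted, and a net-benefit analysis can include covariates.

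**Conclusion.** The point holds as an avoidable loss of precision and an unanswered secondary objective. A common baseline lowers the SE in every variant computed. The size of the gain rests on the plan's variance components, complete data, follow-up at week 27 for the week-scale figures, the intercept-slope covariance, and which contrast the interval describes. No numerical gain is claimed for adding the stratum; it belongs in the model because the trial randomises by it. The gap for objective 4 is textual and does not depend on these assumptions. Its likely low power (50-59% for 3 points under the assumptions shown) is a reason to specify an estimate with an interval, not to leave the analysis out. Baseline adjustment of QALYs is a secondary point, unspecified rather than wrong.

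**What to change.** In the Statistical analysis section, before the primary analysis is run:

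1. Constrain baseline means to be equal across arms: drop the group effect at baseline and keep group x post-baseline time (with linear time, a common intercept and group x time).
2. State that the 90% interval is for the resulting between-arm difference at 3 months, and state the time unit and whether time is categorical or linear.
3. Add referral source and referral source x time. A main effect alone is not enough, because it cancels from a change contrast.
4. Estimate objective 4 from the referral source x time contrast at 3 months with its confidence interval, and treat referral source x group x time as exploratory.

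In the Cost-effectiveness analysis section, state that the QALY difference is adjusted for baseline EQ-5D within each bootstrap replicate.

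The cost is plan wording and a few model terms. Baseline Y-BOCS and EQ-5D are already scheduled before treatment, and referral source is known at randomisation.
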